### Data collection and management

#### Plans for assessment and collection of outcomes {18a}

Preoperative data is collected from the preoperative assessment of the anesthesiologist (medical history, comorbidity, and medication use) and neurosurgeon (surgical indication) available in the electronic patient files. Preoperative patient questionnaires are on paper source documents. Intraoperative data and used materials are collected from the neurosurgical report. Postoperative data during hospitalization is collected from hospitalization reports in the electronic patient files. Data from the outpatient follow-up are available in the electronic files. Postoperative questionnaires are filled out on paper source documents or electronically via RedCap. Data transfer from source documents to the RedCap data collection tool will be done by trained study personnel (research assistant). Regular data quality checks are performed in RedCap to ensure complete and accurate data transfer. Paper source documents will be stored for 10 years after completion of the study in a secure location at the study site.

#### Plans to promote participant retention and complete follow-up {18b}

The 6–12 weeks postoperative outpatient follow-up (FU3) is planned and notified to the patient before hospital discharge. Patients are requested to fill in the questionnaires at the 6–12 weeks postoperative visit (FU3). If the patient is not present at this appointment, or if the clinical follow-up appointment is rescheduled outside the FU3 visit time window (6–12 weeks postoperative), the patient is contacted by telephone to complete the questionnaires within the proposed time window. If this attempt is unsuccessful, the patient is considered lost to follow-up. In case of subject withdrawal, an exit note is added to the electronic case report form (e-CRF) mentioning the withdrawal date and reason of withdrawal.

#### Data management {19}

Data are collected partially on paper source documents (patient questionnaires) and electronic source documents (patient medical records containing surgical and hospitalization reports, registration of used materials). Data is collected by the principal investigator or his designee and locally entered into the e-CRF (RedCap). RedCap is primarily a data collection tool to facilitate post-study analysis based on qualitative data. Access to the e-CRF is strictly regulated and only possible with personal credentials obtained only after successfully completing a specific examination. All data operations are monitored and verified via a tracking system. Entries are verified by double entry (for example manual and automated summary of EQ-5D result); format checks, e.g., integer; and warning messages if data are outside an expected range of values.

As appropriate, baseline characteristics will be reported by mean and standard deviation or number and proportions. The effect of the intervention on the primary outcome will be assessed by comparing the proportion of patients presenting with a postoperative CSF leakage within 12 weeks after surgery.

#### Confidentiality {27}

Patients are identified by their unique study subject number, to ensure the subject’s pseudonymity. All data are processed without identifiable reference to the patient. One secured subject identification list is available in the investigator site file, stored at the study site, containing the code with the study subject number and patient’s name, birth date, and hospital number.

#### Plans for collection, laboratory evaluation, and storage of biological specimens for genetic or molecular analysis in this trial/future use {33}

Not applicable.

### Statistical methods

### Statistical methods for primary and secondary outcomes {20a}

Data will be analyzed in the GraphPad Prism software using a simple *t* test, or non-parametric Mann–Whitney *U* test when not normally distributed, with Bonferroni Holm correction for multiple testing. A *p*-value ˂ 0.05 is considered statistically significant. The primary outcome, i.e., CSF leakage, will be analyzed in terms of a difference in risk between the two treatment groups. The mean difference between the two treatment groups will be reported as a two-sided 95% confidence interval. Secondary endpoints will be calculated using a simple *t* test, non-parametric Mann–Whitney *U* test when not normally distributed, Fisher’s exact test, or chi-squared test, based on the number of events.

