**Fig. 1 Fig1:**
[figure not shown]
Leukocyte- and platelet-rich fibrin (L-PRF) preparation protocol. Top: membrane preparation after blood collection in glass tubes and centrifugation for 12 min (400 g), compression of the fibrin clot. Bottom: liquid L-PRF glue preparation after blood collection in plastic tubes and centrifugation for 3 min (400 g), collection of the upper layer in a sterile syringe

Application of L-PRF would improve wound healing and tissue regeneration, with a reduced infection risk. Apart from the uncomplicated preparation process, the low cost is an additional benefit of L-PRF. The cost of 8 blood tubes is approximately €12, which is very low compared to the price of commercially available fibrin sealants (€100–250) [6].

Given the myriad of theoretical advantages, the use of L-PRF is currently studied in numerous medical disciplines. In neurosurgery, it could play a role in the watertight closure of the dura. The application of L-PRF, in particular, in skull base reconstruction after endoscopic endonasal approaches, has already been described in a few retrospective research articles [7–9]. No major contra-indications were reported for L-PRF in endoscopic endonasal skull base reconstruction or craniectomies. Although L-PRF was reported as a promising biological, studies thus far concluded that larger, prospective trials are warranted to explore the possible applications of L-PRF. This clinical study aims to provide evidence in support of L-PRF in dural closure.

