## Objectives {7}

The general aim of this study is to evaluate the potential of L-PRF in dural closure. More specifically, we are investigating L-PRF as an onlay graft on sutured dura in supratentorial and infratentorial surgeries. We aim to show the non-inferiority of L-PRF compared to the current standard practice. In addition, we want to demonstrate that L-PRF is more cost-effective than standard commercially available fibrin sealants. Risk factors and possible complications will be evaluated to validate safety.

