## Outcomes {12}

The primary endpoint is the success rate of both techniques, which means the absence of a clinically relevant CSF leak at 12 weeks after surgery, i.e., any leak that needs surgical revision or any other intervention, e.g., puncture or aspiration, longer hospitalization, or repeat imaging. The success rate in both groups will be reported in proportions with a 95% confidence interval.

Secondary endpoints include an analysis of peri- and postoperative complications (CSF leakage, both clinically relevant (incisional leakage) and not clinically relevant (swelling, pseudomeningocele), surgical site infection and treatment-site bleeding in particular), as well as a cost-effectiveness evaluation. In addition, the study will compare the efficiency of L-PRF in supratentorial and infratentorial surgery, based on surgical approach and technique.

Peri- and postoperative complications will be obtained from the hospital databases. Each complication requiring additional treatment (surgical revision, intervention, or drug therapy) or investigation (clinical or imaging) or which requires or prolongs hospitalization will be considered. RAND SF-36 questionnaires will be filled out preoperatively (baseline) and 6–12 weeks post-surgery to evaluate patient-reported health concepts such as physical functioning, bodily pain, role limitations due to physical health problems, role limitations due to personal or emotional problems, emotional well-being, social functioning, energy/fatigue, and general health perceptions. The questionnaire is scored as indicated on the official website of RAND, adapted from the scoring described by Ware and Sherbourne [10]. The difference in the change in score to baseline will be compared between the groups, i.e., treated with commercially available fibrin sealants or treated with L-PRF.

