For the cost-effectiveness analysis, the “healthcare payer” perspective will be adopted, which means that all direct treatment-related costs as well as costs related to follow-up will be included in the analysis. For the cost analysis, the following outcomes will be considered: used materials during surgery (units), surgery duration (minutes), intensive care hospitalization time (days/hours), duration of hospitalization (days), associated facility, and staff resources. These data will mainly be retrieved from the hospital records and requested at the hospital’s billing office, if necessary. The most recent unit prices at the time of analysis will be applied. Depending on the primary outcome, i.e., the effectiveness of dural closure, and the clinical effects of both treatments, analysis will be performed as cost-utility or as cost minimization [11, 12]. In addition, the use of EQ-5D-3L to calculate QALYs at 6–12 weeks postoperative will be explored to compare EQ-5D utility scores to other outcomes described above.

The outcomes will be assessed at five study visits within a timeframe of twelve postoperative weeks (Table 2), and a comparison will be made between the two groups considering the change to baseline. Data will be presented as mean and standard deviation or median and interquartile range for continuous variables (including body temperature, °C; blood pressure, mmHg; diameter of craniotomy, mm) and as proportions with 95% confidence intervals for categorical variables (complications, surgical indication, surgical approach). Baseline medical characteristics will be compared between the allocation groups in a similar fashion.

**Table 2 Tab2:** Outcome assessment

Procedure	Visit 1: *screening*	Visit 2: *allocation*	Visit 3: *FU1*^a^	Visit 4: *FU 2*^b^	Visit 5: *FU 3*^c^

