### Methods in analysis to handle protocol non-adherence and any statistical methods to handle missing data {20c}

The results will be analyzed according to the “intention-to-treat” (all randomized participants, irrespective of protocol adherence), “per-protocol” (only participants that were treated according to the protocol), and “as-treated” (all participants according to the treatment they received) principles. These three analyses will be compared to show the possible impact of a lack of data on the results. For the primary endpoint, no missing data are expected. For secondary endpoints (cost-effectiveness evaluation), the predictive mean of the other values within the arm will be used.

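### The test rule for secondary endpoints makes no exception for costs, so skewed costs would be compared by ranks although the payer perspective needs the difference in mean cost

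*Protocol article*

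**What the plan says.** Statistical methods {20a} gives one rule for secondary endpoints: "Secondary endpoints will be calculated using a simple *t* test, non-parametric Mann–Whitney *U* test when not normally distributed", with Fisher's exact or chi-squared tests for event data. The section sets the significance threshold ("value ˂ 0.05 is considered statistically significant") and mentions a Bonferroni–Holm correction for multiple testing. It names no exception.

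Outcomes {12} ends its list of complication endpoints with "as well as a cost-effectiveness evaluation". The section on missing data {20c} classes it the same way: "For secondary endpoints (cost-effectiveness evaluation), the predictive mean of the other values within the arm will be used".

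Outcomes {12} takes the healthcare payer's perspective, "which means that all direct treatment-related costs as well as costs related to follow-up will be included in the analysis". It lists materials, surgery time, intensive care time, hospital days, facility and staff as cost items. It says the analysis will be a cost-utility or a cost-minimization analysis, depending on the primary result, but gives no way of comparing costs between arms. It also allows continuous variables to be summarised by median and interquartile range.

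The aim in Objectives {7} is directional: "we want to demonstrate that L-PRF is more cost-effective than standard commercially available fibrin sealants". Background {6} gives the only prices: "The cost of 8 blood tubes is approximately €12, which is very low compared to the price of commercially available fibrin sealants (€100–250").

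**The concern.** A payer bears the total bill, which is mean cost times the number of patients. Cost minimization compares mean costs, and cost-utility analysis relates a mean cost difference to a mean QALY difference. The Mann–Whitney test addresses something else: whether a randomly chosen L-PRF patient is as likely to cost less as to cost more than a randomly chosen control patient.

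In this trial the two questions can separate in a foreseeable direction. A material saving present in most L-PRF patients shifts many ranks a little. A leak that needs revision surgery or a longer stay affects few patients but adds a large sum to the mean, and a rank test registers only that such a patient is near the top, not by how much. If L-PRF were the cheaper product with more failures, the test would lean towards the conclusion the trial hopes to show.

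**Working it through.** **Inputs from the protocol.** Tubes about €12 against sealant €100–250, so a saving of 100 − 12 = €88 to 250 − 12 = €238, midpoint (88 + 238)/2 = €163. Control success 93.7%, so a 6.3% leak rate. Non-inferiority margin 5 points, so an L-PRF leak rate at the margin of 6.3 + 5 = 11.3%. 167 patients per arm.

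**The plan's own figure.** The protocol gives no figure for the cost comparison. The sample size, which only fixes n here, reproduces: (1.645 + 0.842)² × (0.937×0.063 + 0.95×0.05)/(0.013 + 0.05)² ≈ 166 per arm, or 332, against the stated 334.

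**Break-even, from protocol figures only.** A 5-point excess in leaks cancels the material saving once a leak costs 88/0.05 = €1,760 to 238/0.05 = €4,760.

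**Assumptions.** Cost per leak €10,000. Routine cost lognormal, with the means and SDs shown in the table. The protocol gives none of these.

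**Model.** Control cost = routine cost + saving forgone + €10,000 × leak. L-PRF cost = routine cost + €10,000 × leak. For equal means the L-PRF leak rate is 6.3% + 163/10,000 = 7.9%. With L-PRF at the margin, its true mean is 0.05 × 10,000 − 163 = €337 higher. Each setting has 2,000 simulated trials, with two-sided tests at 0.05, counting only significant results in the direction of L-PRF being cheaper (nominal 2.5%). Ranges are across repeated runs.

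| Routine cost: mean / SD | Mann–Whitney, equal means | Mann–Whitney, L-PRF €337 dearer |
|---|---|---|
| €4,000 / €300 | 97–98% | 90% |
| €4,000 / €500 | 62–64% | 37–40% |
| €4,000 / €1,000 | 17–20% | 6–7% |
| €4,000 / €1,500 | 10% | – |
| €8,000–12,000 / €2,000–8,000 | about 3–7% | 0.9–1.7% |

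Welch's test on means gives 2–3% at equal means for SDs of €300–3,000. With L-PRF €337 dearer it gives at most 0.2% at SDs of €300–1,000.

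**Sensitivity to the saving** (equal means). At SD €1,000 the Mann–Whitney rate is 8% for an €88 saving and 36% for €238.

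**Effect of a multiplicity correction.** At an illustrative level of 0.01 (five tests, assumed), the equal-means rate with the €163 saving falls from 62% to 37% at SD €500, from 20% to 6% at SD €1,000, and from 5% to 0.8% at SD €3,000.

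**Independent variant.** With 175 per arm, mean routine cost €8,000 and L-PRF at the margin, the true L-PRF mean is 500 − 88 = €412 or 500 − 238 = €262 higher. Mann–Whitney calls L-PRF cheaper in 2% and 18% of trials at SD €1,000, and in 1% and 2% at SD €3,000. Welch does so in at most 0.7%.

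**The case against.** The strongest reply is that the link is inferred. Statistical methods {20a} never mentions costs, and its wording, "test when not normally distributed, Fisher’s exact test, or chi-squared test, based on the number of events", reads like a list for clinical endpoints. The economic evaluation has its own paragraph, and neither a cost-utility nor a cost-minimization analysis is a two-group rank test. No passage says the cost-effectiveness claim will rest on a p-value for cost. A health-economic plan that is not shown could set another method. This stands in part: the protocol does not explicitly assign costs to Mann–Whitney, and it would be wrong to say that it does. But the protocol twice classes the evaluation as a secondary endpoint, gives a rule for secondary endpoints and states no exception. That is a stated rule that misses the target, not a detail left open.

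The second reply concerns size, and it largely succeeds. A reader might infer from the top rows of the table that a false finding of lower cost is likely. Those rows need an SD of €300–500 on a mean of €4,000, which is 8–13% of the mean. The trial mixes tumour, vascular and functional surgery and counts intensive care and hospital days, so costs that uniform are implausible. A nearly symmetric routine cost also sits badly with the skewness that would trigger the rank test.

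The saving may be smaller than €88–238 too. The €12 covers blood tubes only, other L-PRF materials and staff time are also costed, and L-PRF patients may receive commercial sealant for haemostasis or fixation.

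A reader might also infer that the test rejects however expensive the extra leaks are. At SDs of €2,000–8,000 that is not so: with L-PRF €337 dearer, the rate is below nominal.

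**Conclusion.** The point holds as a mismatch between test and question. As written, non-normal costs fall under a rank test, while the stated perspective and both planned types of economic analysis need mean cost. That is true whatever the error rates turn out to be, because a Mann–Whitney p-value neither estimates nor tests the mean difference.

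The practical harm is moderate and uncertain. Assuming €10,000 per leak and a €163 saving, the rate of falsely declaring L-PRF cheaper at equal means is about 17% at a routine-cost SD of €1,000, 10% at €1,500 and 3–7% at €2,000–8,000, against 2.5% nominal, and lower after the Holm correction. The documents do not support a claim that the cost conclusion will probably be wrong. The point touches one secondary endpoint and leaves the primary non-inferiority analysis unaffected.

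**What to change.** Add to Statistical methods {20a}: costs are exempt from the Mann–Whitney rule and are compared as the difference between arms in arithmetic mean cost per patient, with a 95% confidence interval from Welch's method or a non-parametric bootstrap. Medians and interquartile ranges of cost are descriptive only. If a separate health-economic plan already says this, a cross-reference is enough.

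The cost is one sentence, with no change to data collection or conduct. Welch's test is available in GraphPad Prism, the software named in the protocol; the bootstrap needs other software. Intervals for mean cost will be wider than a rank test would suggest, and that width is the real uncertainty about the payer's bill.

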### Interim analyses {21b}

Per protocol, no interim analyses will be performed.

### Methods for additional analyses (e.g., subgroup analyses) {20b}

Subgroup analyses will be performed for surgical indication (tumor, vascular or functional), craniotomy diameter (small: ˂ 30 mm; medium: ˃ 30 mm; ˂ 80 mm; and large: ˃ 80 mm) recurrent surgery, patient age, gender, medication use, and alcohol and smoking habits. The data will be statistically tested using a simple *t* test or Mann–Whitney *U* test, or Fisher’s exact test or chi-squared test depending on normality, type of variable, and number of events. We do not intend to perform adjusted analyses.

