### Sample size {14}

Sample size calculation was performed according to the primary outcome, using an online power calculator for binary outcome non-inferiority trials (Sealed Envelope Ltd. available from: www.sealedenvelope.com). This is a non-inferiority trial with a binary outcome using a one-sided alpha of 0.05 and 80% power. The assumed success rate is 93.7% in the control arm, based on center-specific experience as well as the literature [13]. Data on the use of L-PRF for this indication is limited, but we assume a 95% success rate based on a prior feasibility study [9].

The statistical hypothesis for testing the treatment difference is presented as follows: H_0_: Δ ≤  − 0.05 tested against the alternative hypothesis and H_A_: Δ >  − 0.05, where Δ is the difference between the success rates of experimental and control condition and − 0.05 is the non-inferiority difference. The non-inferiority limit was set at 0.05 considering (1) reported CSF leakage rates without commercially available fibrin sealant averaging 17.2% [14] and (2) important additional benefits of L-PRF compared to commercially available fibrin sealants including the completely autologous nature (eliminating immune reactions), presence of immunologic cells and reduced costs.

Based on this power calculation, 334 patients need to be included, 167 in each group. A drop-out rate of 2–5% is expected due to loss of follow-up and non-adherence to the allocation or failure of L-PRF preparation. Therefore, 350 patients will be enrolled, 175 in each group.

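### Subgroup analyses over eight factors, and the supra- versus infratentorial comparison, rest on simple two-group tests that do not test whether the L-PRF effect differs between subgroups

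*Protocol article*

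**What the plan says.** Protocol article, Methods for additional analyses {20b}: subgroup analyses are planned for surgical indication, craniotomy diameter, recurrent surgery, age, gender, medication use, alcohol and smoking, which makes eight factors. The tests are the t test or Mann-Whitney, or Fisher's "exact test or chi-squared test depending on normality, type of variable, and number of events". The section then states that no adjusted analyses are intended. It names no interaction test and does not call the analyses exploratory. The diameter classes are below 30 mm, above 30 and below 80 mm, and above 80 mm.

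Outcomes {12} adds, among the secondary aims, that "the study will compare the efficiency of L-PRF in supratentorial and infratentorial surgery, based on surgical approach and technique". Surgical approach is not in the {20b} list. The tests for secondary endpoints are in Statistical methods {20a}, and they are the same simple two-group tests. That section also mentions a Bonferroni-Holm correction for multiple testing; {20b} does not repeat it.

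Background {6} gives average leak rates of 2.9% for supratentorial and 5.8% for infratentorial procedures.

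**The concern.** A subgroup analysis in a randomized trial asks whether the difference between arms changes with a patient characteristic. The article does not say how its tests are set up, but neither possible reading answers that question.

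- **Arms compared within each level.** Each level gets its own p-value, and the reader is left to set a significant level against a non-significant one. That contrast is not a test of a different effect. These are also tests of difference, so a non-significant result in a sparse stratum is easily mistaken for equal performance.
- **Levels compared with each other.** This shows who leaks more often, which is prognosis and not treatment effect. The wording of the site aim leans this way. Supra- and infratentorial patients are not randomized groups, and their background rates already differ (2.9% versus 5.8%). L-PRF could therefore look less effective infratentorially although its effect relative to sealant is the same at both sites.

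At stake are the statements about where L-PRF does well or badly. The article's Discussion expects the results to influence practice in dural closure, and site- or indication-specific statements would be part of that.

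A smaller, separate fault is that a craniotomy of exactly 30 mm or 80 mm falls in no diameter class.

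**Working it through.** **Inputs, all from Sample size {14}.** "The assumed success rate is 93.7% in the control arm" (leak rate 6.3%). For L-PRF, "we assume a 95% success rate based on a prior feasibility study" (leak rate 5.0%). "The non-inferiority limit was set at 0.05". The calculation is made "using a one-sided alpha of 0.05 and 80% power". Result: "334 patients need to be included, 167 in each group". "A drop-out rate of 2–5% is expected", and enrolment is set at 350, 175 per arm.

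**The plan's own figure.** n per arm = (0.937×0.063 + 0.95×0.05) × (1.645 + 0.842)² / (0.05 + 0.013)² = 165.9, so 166. The pooled-variance form gives 166.1, so 167. The stated 167 per arm is reproduced.

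**Expected leaks.** 175×0.063 + 175×0.05 = 11.0 + 8.8 = 19.8 in 350 patients.

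**Precision within a subgroup.** The article gives no subgroup prevalences, so the sizes below are assumptions.

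| Subgroup share | Per arm | Rates used | 95% CI half-width of the risk difference |
|---|---|---|---|
| one half | 87.5 | 5.65% in both arms | 1.96×√(2×0.0565×0.9435/87.5) = 6.8 points |
| one third | 58 | 6.3% and 5.0% | 1.96×√(0.063×0.937/58 + 0.05×0.95/58) = 8.4 points |
| one fifth | 35 | 5.65% in both arms | 1.96×√(2×0.0565×0.9435/35) = 10.8 points |

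All three exceed the 5-point margin. At 58 per arm, exact two-sided Fisher power for a doubling from 6.3% to 12.6% is 12%.

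**False positives, if arms are compared within levels without adjustment and the tests are independent.** Eight two-level factors give 16 tests. With three levels for indication and for diameter, and two levels assumed for the other six, there are 18.

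- *Exact calculation for Fisher.* With a 5.65% leak rate in both arms, the true size of a nominal 5% test is 1.2% at 58 per arm and 2.0% at 88 per arm. Over 16 tests: 1 − 0.988^16 = 18% and 1 − 0.980^16 = 28%.
- *Simulation.* 1,500 trials per scenario, 18 tests, no true subgroup effect, splits assumed at 60/20/20 for the three-level factors and 50/50 for the others. At least one p < 0.05 occurs in 29–30% of trials with Fisher and in 43–45% with chi-squared. In nearly all of these, one level is significant and another level of the same factor is not.
- *With Holm across the 18 tests.* About 1–2%.

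**What an interaction test could show.** For a binary factor split 50:50 (assumed), the standard error of the difference between two risk differences is √(4×0.0565×0.9435/87.5) = 4.9 points. For 80% power at two-sided 0.05, the interaction must be (1.96 + 0.84) × 4.94 = 13.8 points, more than twice the overall leak rate of about 5.7%.

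**The case against.** **Holm already controls the error.** This stands in part. If the correction in {20a} extends to {20b}, false positives fall to about 1–2%, so it would be wrong to say that the plan has no error control. Its scope over the subgroup tests is simply not stated. Holm also does not make a two-group test answer the interaction question, and it does not stop non-significance being taken as equality.

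**The false-positive risk is often overstated.** A reader might compute 1 − 0.95^16 = 56%. That gives every test a true size of 5%, which Fisher's test does not have with so few events. As {20b} lets the number of events guide the choice of test, sparse strata would usually go to Fisher, where the figure is roughly 18–30%.

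**The section may describe a risk-factor comparison.** This is possible. The Objectives mention evaluating risk factors, and a t test suits age in leakers versus non-leakers better than it suits a binary leak outcome. On that reading no claim about differing treatment effects is planned. But then the analyses are not subgroup analyses of treatment, and the text should say so. The site aim is ambiguous in the same way.

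**Interaction tests are weak too.** True. Eight unadjusted interaction tests still gave at least one p < 0.05 in about 25–27% of the simulated trials. This is a reason to estimate and to label the results exploratory, not a reason to keep tests of a different question.

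**Such details belong in an analysis plan.** That would hold if the article were silent. It names the tests and excludes adjusted analyses.

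**Conclusion.** The point holds as a matter of method: the tests named in {20a} and {20b} do not assess whether the L-PRF effect differs by subgroup or by surgical site, on either reading of the text. With about 20 expected leaks, the consequence is a risk of misleading subgroup statements, not a certainty. The chance of at least one false positive is about 18–30% (Fisher) or 43–45% (chi-squared) if arms are compared within levels without adjustment, and about 1–2% if Holm applies. These figures rest on assumed subgroup splits, independent factors and the planning leak rates.

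Two stronger inferences are not supported. The article plans no non-inferiority claim within a subgroup; its hypothesis in {14} concerns the overall difference only. And the primary non-inferiority conclusion is not affected. This should be corrected, but it does not threaten the trial's main result.

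**What to change.** 1. In {20b}, for each factor report the risk difference by level with its 95% CI, plus one treatment-by-factor interaction estimate and test. Label these analyses exploratory, and give no within-subgroup p-values or non-inferiority claims.
2. In {12}, recast the supra- versus infratentorial aim as a treatment-by-approach interaction.
3. State whether the Holm correction in {20a} covers these tests.
4. Close the diameter classes so that exactly 30 mm and exactly 80 mm each belong to one class.

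The cost is wording and a similar analysis effort, with the same data and no extra patients. The statement excluding adjusted analyses should be reworded so that it does not appear to bar an interaction term. The downside is low power: with an even split, only an interaction of about 13.8 points would be detected with 80% power, so the results support estimation and not decisions about individual subgroups.
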